## IV Synopsis

**Title:** Safety and efficacy of a single subretinal injection of rAAV.hCNGA3 in patients with CNGA3-linked achromatopsia investigated in an exploratory, dose-escalation trial

**Phase:** I/II

**Indication:** CNGA3-linked achromatopsia

**Aim:** To proof the safety and efficacy of rAAV.hCNGA3 in patients with achromatopsia

**Study design:** open, mono-center trial with fellow-eye comparison

### Study Population:

#### Inclusion Criteria (Study Eye)

- clinical diagnosis of achromatopsia
- $\geq 18$  years of age
- confirmed mutation in CNGA3
- BCVA  $\geq 20/400$
- a minimal outer nuclear layer thickness of  $10\mu\text{m}$  at  $3^\circ$  eccentricity in the study eye (normal =  $38\pm 6\mu\text{m}$ )
- ability to understand and willingness to consent to study protocol
- no infection with Human Immunodeficiency Virus (HIV)
- negative pregnancy test in women with childbearing potential (a woman who is two years post-menopausal or surgically sterile is not considered to be of childbearing potential)

#### Exclusion Criteria

- additional interfering eye conditions (e.g. uveitis, advanced cataract) in the study eye
- systemic conditions (e.g. coronary heart disease, autoimmune disorders) which may affect study participation or outcome measures
- current or recent participation in other study/or administration of biologic agent within the last three months
- recent (6 months) ocular surgery, intravitreal or subretinal implantation of a medical device
- known sensitivity to any compound used in the study
- contraindications to systemic immunosuppression
- subject/partner of childbearing potential unwilling to use adequate contraception for four months

- nursing or pregnant women
- any other cause that, in the investigator's opinion, renders potential subjects not suitable for the study
- mutations in another achromatopsia gene
- contraindications in view of the planned surgery (e.g. anaemia Hb<8g/dl, severe coagulopathy, severe blood pressure fluctuations)
- ocular opacity and mature cataract
- ocular infection with herpes simplex virus in medical history
- history of ocular malignancies
- disorders of the internal retina (e.g. retinal detachment in the patients history)
- glaucoma defined as damage of the optic nerve
- vascular retinal occlusion
- diabetic patients suffering from retinopathy and/or macula edema
- patients treated with oral corticoids within 14 days prior inclusion
- systemic illness or medically significant abnormal laboratory values in blood analysis including renal and hepatic functions at inclusion
- absence of vision on the other contralateral eye

**Patient Number:** Nine patients will be assigned to three cohorts of three patients respectively.

#### **Treatment:**

Each cohort will receive a different, increasing dosage of viral vector genome particles. Three cohorts of patients are planned with low, medium and high dose administration levels up to  $1 \times 10^{11}$  of rAAV8 incorporating the therapeutic expression cassette.

After standard three-port 23G pars plana vitrectomy, balanced salt solution will be used to induce a localized primary retinal detachment in a controlled fashion. Vector solution will be applied using disposable 41G extendible subretinal injection needles within a standard 23G body to fit the port system. Administration will be unilateral (worse eye) in each patient.

**Primary Endpoint:** Safety as the primary endpoint will be assessed by clinical examination of ocular inflammation (slit lamp, fundus biomicroscopy, angiography, perimetry or electrophysiology). Systemic safety will be assessed by vital signs, routine clinical chemistry testing (including CRP, ESR) and full/differential blood counts. Immunopathology essays will include specific enzyme-linked immunosorbent assays for humoral antibodies against rAAV8 capsid protein. Biodistribution will be monitored by polymerase chain reaction studies on rAAV8 genome in blood, urine, saliva and lachrymal fluid.

**Statistical Methods:** AEs and SAEs will be documented using line listings and tabulations (MetraCad code will be applied). Descriptive analysis will include line charts for individual patients. Standard errors and means will also be displayed using line charts. This will be done for the raw measurements and for the difference between treated and untreated control eye within each patient.

Descriptive parameters will be given for the full cohort (n=9) but not for the sub-cohorts (n=3). Additionally correlation analysis will be performed in a purely descriptive manner for the comparison of subjective and objective measurements. For each subject and measurement, the delta of the value for the interventional eye minus the mean of control eye values over time will be determined. In scatter plots for pairs of variables (measurements pooled over subjects) the association between these deltas will be displayed.

**Time Schedule:** Start of trial November 2015, end of recruitment November 2016, end of trial November 2017, duration of trial per patient: one year with four years of follow-up.

[figure not shown]

## VI Synopsis in German / Deutsche Prüfplan-zusammenfassung

**Titel:** Sicherheit und Wirksamkeit einer einzelnen subretinalen Injektion von rAAV.hCNGA3 bei Patienten mit CNGA3-chromosomaler Achromatopsie, untersucht in einer explorativen Studie mit ansteigender Dosierung.

**Phase:** I/II

**Indikation:** CNGA3-chromosomale Achromatopsie

**Ziel:** Nachweis der Sicherheit und Wirksamkeit von rAAV.hCNGA3 in Patienten mit Achromatopsie

**Studiendesign:** Offene monozentrische Studie mit Vergleich zum Partnerauge

### Studienpopulation:

#### Einschlusskriterien (Studienauge)

- Klinisch diagnostizierte Achromatopsie
- Alter  $\geq 18$  Jahre
- Bestätigte Mutation in CNGA3
- bestkorrigierte Sehschärfe  $\geq 20/400$
- minimale äußere nukleäre Schichtdicke von 10  $\mu\text{m}$  bei 3° Exzentrität im Studienauge (normal =  $38 \pm 6 \mu\text{m}$ )
- Fähigkeit das Studienprotokoll zu verstehen und in die Teilnahme einzuwilligen
- Keine Infektion mit dem Humanen Immundefizienz-Virus (HIV)
- Negativer Schwangerschaftstest bei gebärfähigen Frauen (Frauen 2 Jahre nach Beginn der Menopause oder operativ sterilisierte Frauen zählen als nicht gebärfähig).

#### Ausschlusskriterien

- Zusätzliche Augenkrankheiten (z.B. Uveitis, fortgeschrittener Katarakt) im Studienauge
- systemische Begleiterkrankungen (z.B. Koronare Herzkrankheiten, Autoimmunerkrankungen), die für die Studienteilnahme als wesentlich erachtet werden
- Aktuelle oder kürzliche Teilnahme an einer anderen klinischen Studie und/oder Einnahme biologischer Agenzien innerhalb der letzten 3 Monate
- Kürzliche (6 Monate) Augenoperation, intravitreale oder subretinale Implantation eines Medizinproduktes
- Bekannte Unverträglichkeit gegenüber einer in der Studie eingesetzten Substanz
- Kontraindikationen zur systemischen Immunsuppression

- Gebärfähige Patienten oder Partner, die nicht zur Empfängnisverhütung für vier Monate bereit sind
- Stillende oder schwangere Frauen
- Andere Gründe, die nach Meinung des Prüfers gegen die Eignung eines Probanden sprechen
- Mutation in einem anderen Achromatopsie-Gen
- Kontraindikationen bezogen auf die geplante Operation (z.B. Anämie, Hb<8g/dl, schwere Koagulopathie, starke Blutdruckschwankungen)
- Trübung der optischen Medien und fortgeschrittene Katarakt
- Okuläre Herpes Simplex Infektion in der Krankengeschichte
- Okuläre Tumoren in der Krankengeschichte
- Erkrankungen der inneren Netzhaut (z.B. Netzhautablösung in der Krankengeschichte)
- Glaukom mit Schädigung des Sehnerven
- Gefäßverschluss in der Netzhaut
- Diabetiker, die unter Retinopathie und/oder Makulaödem leiden
- Patienten, die innerhalb von 14 Tage vor Studieneinschluss mit oralen Kortikoiden behandelt wurden
- Systemische Erkrankung oder klinisch relevant abweichende Laborwerte einschließlich Nieren- und Leberwerten bei Studieneinschluss
- fehlende Sehfunktion des Partnerauges

**Anzahl der Patienten:** Neun Patienten werden 3 Kohorten mit je 3 Patienten zugeordnet.

### Behandlung:

Jede Kohorte wird eine andere Dosierung des viralen Vektor-genom-Partikels erhalten. Drei Patientenkohorten sind geplant mit niedriger, mittlerer und hoher Dosierung bis zu  $1 \times 10^{11}$  vgp des rAAV8.

Nach Standard 3-Port 23G pars-plana-Vitrektomie wird Salzlösung eingesetzt, um eine kontrollierte, lokale, primäre Netzhautablösung zu induzieren. Die Vektorlösung wird mittels 41G erweiterbarer subretinaler Einwegs-Injektionsnadel mit einem Standard 23G Korpus, passend zum Port-System, eingebracht. Die Gabe wird bei jedem Patient unilateral vorgenommen (schlechteres Auge).

### Primärer Endpunkt:

Die Sicherheit als primärer Endpunkt wird durch klinische Untersuchung der okulären Entzündung (Spaltlampe, Funduskopie, Angiographie, Perimetrie oder Elektrophysiologie) beurteilt. Systemische Sicherheit wird durch Vitalparameter, routinemäßige klinische Chemie (einschließlich CRP, BSG) und Voll-/Differentialblutbild beurteilt. Als immunpathologisches Nachweisverfahren dient das spezifische antikörpergekoppelte Nachweisverfahren ELISA (enzyme-linked immunosorbent assay) für humorale Antikörper gegen das rAAV8 Capsid-Protein, um die zelluläre Immunantwort gegen das rAAV8 Capsid-Protein zu überwachen. Die Biodistribution

[figure not shown]

3204 wird durch Polymerase-Kettenreaktion (PCR)-Untersuchungen über das rAAV8  
3205 Genom in Blut und Urin überwacht werden.

3206

3207 **Statistische Methoden:**

3208 Deskriptive Statistik ist geplant.

3209

3210 **Zeitplan:** Studienstart November 2015, Ende der Rekrutierung November 2016,  
3211 Studienende November 2017, Dauer der Studie pro Patient: ein Jahr mit  
3212 anschließend vier Jahren Nachbeobachtungsphase.

3213

3214

3215 **VII Flowchart of Visits and Procedures**

3216

3217 See next page

| Flowchart of Visits and Procedures CNGA3 Trial |                                                                   |               |     |    |    |         |          |          |          |          |                      |           |           |           |           |
|------------------------------------------------|-------------------------------------------------------------------|---------------|-----|----|----|---------|----------|----------|----------|----------|----------------------|-----------|-----------|-----------|-----------|
|                                                | Visit (no)                                                        | 1             | 2   | 3  | 4  | 5       | 6        | 7        | 8        | 9        | 10                   | Fup 1     | Fup2      | Fup3      | Fup 4     |
|                                                | Date                                                              | Screening     | D 0 | D1 | D2 | D3      | D14      | D30      | D90      | D180     | D365, Close out / ET | M24       | M36       | M48       | M60       |
|                                                | Time window                                                       | day -30 to -2 |     |    |    | ± 1 day | ± 3 days | ± 5 days | ± 7 days | ± 7 days | ± 14 days            | ± 1 month | ± 1 month | ± 1 month | ± 1 month |
|                                                | Procedure                                                         |               |     |    |    |         |          |          |          |          |                      |           |           |           |           |
| 1.                                             | Medical /surgical/ history                                        | x             |     |    |    |         |          |          |          |          |                      |           |           |           |           |
| 2.                                             | Ocular / surgical/ history                                        | x             |     |    |    |         |          |          |          |          |                      |           |           |           |           |
| 3.                                             | BMI                                                               | x             |     |    |    |         |          |          |          |          | x                    |           |           |           |           |
| 4.                                             | Vital signs                                                       | x             | x   | x  | x  | x       | o        | o        | o        | o        | x                    | o         | o         | o         | o         |
| 5.                                             | Urine pregnancy test                                              | x             | x   |    |    |         | x        | x        | x        | x        | x                    |           |           |           |           |
| 6.                                             | Hematology/basic chemistry/urine analysis                         | x             | o   | o  | o  | x       | x        | o        | o        | x        | x                    | x         | x         | x         | x         |
| 7.                                             | CRP, IgG, IgM                                                     | x             |     |    | x  | x       | x        | x        | o        | o        | o                    | o         | o         | o         | o         |
| 8.                                             | Immunopathology a                                      | x             |     |    |    |         |          | x        | x        | o        | o                    | o         | o         | o         | o         |
| 9.                                             | PCR of rAAV8 genome                                               | x             |     |    |    | x       | x        | o        | o        | o        | o                    | o         | o         | o         | o         |
| 10.                                            | Best corrected visual acuity                                      | x             |     |    |    |         | x        | x        | x        | x        | x                    | x         | x         | x         | x         |
| 11.                                            | Basic ophthalmological exam (miosis)                              | x             | x   | x  | x  | x       | x        | x        | x        | x        | x                    | x         | x         | x         | x         |
| 12.                                            | Contrast sensitivity (PR charts)                                  | x             |     |    |    |         | x        | x        | x        | x        | x                    | x         | x         | x         | x         |
| 13.                                            | Flicker fusion frequency                                          | x             |     |    |    |         |          | x        | x        | x        | x                    |           |           |           |           |
| 14.                                            | Colour constancy (chromatic adaptation) e              | x             |     |    |    |         |          | o        | o        | x        | x                    | o         | o         | o         | o         |
| 15.                                            | Anomaloscopy e                                         | x             |     |    |    |         | x        | x        | x        | x        | x                    | o         | o         | o         | o         |
| 16.                                            | Cambridge Colour Test (CCT) e / Panel D15 f | x             |     |    |    |         | x        | x        | x        | x        | x                    | o         | o         | o         | o         |
| 17.                                            | IR-Video-Pupillography                                            | x             |     |    |    |         |          | x        | x        | x        | x                    | o         | o         | o         | o         |
| 18.                                            | MP-1 Microperimetry (20°)                                         | x             |     |    |    |         |          | x        | x        | x        | x                    | x         | x         | x         | x         |
| 19.                                            | Fundoscopy (mydriasis)                                            | x             | x   | x  | x  | x       | x        | x        | x        | x        | x                    | x         | x         | x         | x         |
| 20.                                            | Dark adaptation test                                              | x             |     |    |    |         |          | x        | x        | x        | x                    | o         | o         | o         | o         |
| 21.                                            | ff-ERG (scotopic and photopic)                                    | x             |     |    |    |         |          | x        |          | o        | x                    | o         | o         | o         | o         |
| 22.                                            | sdOCT                                                             | x             | o   | o  | o  | o       | x        | x        | o        | o        | x                    | x         | x         | x         | x         |
| 23.                                            | Fundus autofluorescence                                           | x             |     |    |    |         | x        | x        | o        | o        | x                    | x         | x         | x         | x         |
| 24.                                            | Fundus photography                                                | x             |     |    |    |         | x        | x        | x        | o        | x                    | x         | x         | x         | x         |
| 25.                                            | ICG (Indocyanin green) angiography                                | x             |     |    |    |         | o        | o        | x        | o        | x                    | o         | o         | o         | o         |
| 26.                                            | Systemic steroids b                                    | x (Day -1)    | x   | x  | x  | x       |          |          |          |          |                      |           |           |           |           |
| 27.                                            | Topical steroids and antibiotics c                     | x (Day -1)    | x   | x  | x  | x       | x        | x        |          |          |                      |           |           |           |           |
| 28.                                            | Subretinal injection of rAAV8 vector                              |               | x   |    |    |         |          |          |          |          |                      |           |           |           |           |
| 29.                                            | VFQ25                                                             | x             |     |    |    |         |          | x        |          | x        | x                    | o         | o         | o         | o         |
| 30.                                            | Psychiatric examination                                           | x             |     |    |    |         |          |          |          |          |                      |           |           |           |           |
| 31.                                            | Brief Symptom Inventory (BSI)                                     | x             |     |    |    |         | x        | x        | x        | x        | x                    |           |           |           |           |
| 32.                                            | Psychological counselling d                            |               | x   | x  | x  | x       | x        | x        | x        | x        | x                    |           |           |           |           |
| 33.                                            | study specific scale, A3-PRO                                      |               |     |    |    |         | x        | x        | x        | x        | x                    | x         | x         | x         | x         |
| 34.                                            | Adverse event recording                                           |               | x   | x  | x  | x       | x        | x        | x        | x        | x                    | x         | x         | x         | x         |
| 35.                                            | Concomitant medication                                            | x             | x   | x  | x  | x       | x        | x        | x        | x        | x                    | x         | x         | x         | x         |
| 36.                                            | HIV Test                                                          | x             |     |    |    |         |          |          |          |          |                      |           |           |           |           |

o: optional, if control deemed necessary by investigator

a including but not limited to: Anti-AAV8 capsid ELISA

b Systemic steroids will be given orally 1.0mg/kg for appr. three weeks starting at day -1 and then tapered off after day 19 as deemed appropriate by the investigator (e.g. 40/30/20/15/10mg).

c Moxifloxacin eye drops 0.5% 4x/d & 0.1% dexamethasone gel 4x/d for 21d starting at day -1

d at patient's need and discretion

e if the previous tests have shown improved results

f if CCT is not feasible

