### D90 (± 7 days)

- 4325 - Vital signs (O)
- 4326 - Urine pregnancy test
- 4327 - Hematology/ basic chemistry (O)
- 4328 - CRP, IgG, IgM (O)
- 4329 - Immunopathology
- 4330 - PCR of rAAV8 genome (O)
- 4331 - Visual Acuity, BCVA (ETDRS)
- 4332 - Basic ophthalmological exam
- 4333 - Contrast sensitivity (PR charts)
- 4334 - Flicker Fusion Frequency
- 4335 - Colour Constancy (chromatic adaption) (O)
- 4336 - Anomaloscopy
- 4337 - Cambridge Colour Test / Farnsworth D15
- 4338 - IR Video Pupillography
- 4339 - MP-1 Microperimetry (20°)
- 4340 - Funduscopy (mydriasis)
- 4341 - Dark adaptation test
- 4342 - ff-ERG (scotopic and photopic) (O)
- 4343 - sdOCT (O)
- 4344 - FAF (O)
- 4345 - FF
- 4346 - Angiography
- 4347 - Brief Symptom Inventory (BSI)
- 4348 - Psychological counselling
- 4349 - Study specific scale, A3-PRO
- 4350 - Adverse event recording
- 4351 - Concomitant medication
- 4352

[figure not shown]**Visit 9****D180 ( $\pm$  7 days)**

- Vital signs (O)
- Urine pregnancy test
- Hematology/ basic chemistry
- CRP, IgG, IgM (O)
- Immunopathology (O)
- PCR of rAAV8 genome (O)
- Visual Acuity, BCVA (ETDRS)
- Basic ophthalmological exam
- Contrast sensitivity (PR charts)
- Flicker Fusion Frequency
- Colour Constancy (chromatic adaption)
- Anomaloscopy
- Cambridge Colour Test / Farnsworth D15
- IR Video Pupillography
- MP-1 Microperimetry (20°)
- Funduscopy (mydriasis)
- Dark adaptation test
- ff-ERG (scotopic and photopic) (O)
- sdOCT (O)
- FAF (O)
- FF (O)
- Angiography (O)
- VFQ25
- Brief Symptom Inventory (BSI)
- Psychological counselling
- Study specific scale, A3-PRO
- Adverse event recording
- Concomitant medication

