**Visit 10****D365, Close out ( $\pm$  14 days)**

- BMI
- Vital signs
- Urine pregnancy test
- Hematology/ basic chemistry
- CRP, IgG, IgM (O)
- Immunopathology (O)
- PCR of rAAV8 genome (O)
- Visual Acuity, BCVA (ETDRS)
- Basic ophthalmological exam
- Contrast sensitivity (PR charts)
- Flicker Fusion Frequency
- Colour Constancy (chromatic adaption)

[figure not shown]

- 4399 - Anomaloscopy
- 4400 - Cambridge Colour Test / Farnsworth D15
- 4401 - IR Video Pupillography
- 4402 - MP-1 Microperimetry (20°)
- 4403 - Funduscopy (mydriasis)
- 4404 - Dark adaptation test
- 4405 - ff-ERG (scotopic and photopic)
- 4406 - sdOCT
- 4407 - FAF
- 4408 - FF
- 4409 - Angiography
- 4410 - VFQ25
- 4411 - Brief Symptom Inventory (BSI)
- 4412 - Psychological counselling
- 4413 - Study specific scale, A3-PRO
- 4414 - Adverse event recording
- 4415 - Concomitant medication
- 4416

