## 8.4. Non-ophthalmological and ophthalmological Procedures

All procedures should be performed in the sequence given by the flowchart, whenever possible. If feasible, the same investigators should perform the examinations for the study duration. Advanced test procedures, such as, but not limited to BCVA, microperimetry and pupillography, will be performed by study personnel after method-specific training.

If not specified differently, all tests described here will be performed according to the Flowchart of Visits and Procedures in *both* eyes.

All ophthalmological procedures will be performed in a fixed sequence, testing the study eye first and the fellow eye afterwards.

[figure not shown]

More details of all examination procedures can be found in the Procedure Manual in its current version as approved by the Principal Investigator.

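### Flowchart footnote e makes three post-baseline colour-vision tests conditional on earlier improvement, which conflicts with section 8.2 and, if followed, tilts their planned averages towards benefit.

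*Supplement*

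**What the plan says.** The current protocol has two schedules for the colour-vision tests.

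- **Flowchart (section VII).** Rows 14 to 16 read "Colour constancy (chromatic adaptation) e", "Anomaloscopy e" and "Cambridge Colour Test (CCT) e / Panel D15 f". Footnote e is "if the previous tests have shown improved results". Footnote f makes the D15 panel the fallback when the Cambridge test is not feasible.
- **Visit lists (section 8.2).** Anomaloscopy and "Cambridge Colour Test / Farnsworth D15" appear at D14, D30, D90, D180 and D365 with no condition. Colour constancy is optional at D30 and D90 and unconditional at D180 and D365.
- **Link between them (section 8.4).** Unless something different is specified, "all tests described here will be performed according to the" flowchart, in both eyes.

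Section 7.1 lists all three tests as secondary endpoints. Section 10.4 plans individual line charts, means and standard errors for raw values and for the difference between eyes, descriptive parameters for all nine patients, and scatter plots of pairs of measurements. Section 10.1 says there is no blinding.

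**The concern.** If footnote e is applied, whether a colour outcome is measured after baseline depends on how the patient has done so far, as judged by staff who know which eye was treated. There are two readings of the footnote, and both select on outcome. If the previous tests are the earlier rows of the flowchart at the same visit, colour is measured only in patients who gained on measures such as acuity, contrast or flicker. If they are the same test at an earlier visit, a patient without an early gain is not retested, and a late response would be missed.

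Absent colour perception is the first symptom listed in section 1.1.1, and better colour discrimination is a named potential benefit in section 7.5. Section 10.5 adds an interim analysis in the course of negotiations with industrial sponsors about later development. A descriptive colour summary taken from patients picked for improvement could therefore be read as evidence of a gain. No later analysis can recover tests that were not done.

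**Working it through.** **1. Reach of the condition.** At screening no earlier study test exists, so footnote e can act only after baseline. From D14 (anomaloscopy, Cambridge test) or D30 (colour constancy), the flowchart applies it and section 8.2 does not.

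**2. Which schedule governs.** Section 8.4 defers to the flowchart unless something different is specified. Section 8.2 could count as such a specification, because it carries over the optional marks for other tests. It could also be a shortened list, because it leaves out footnotes d and f as well as e. The text does not settle the matter.

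**3. Figures in the plan.** Section 10.2 states that no sample size was calculated, so there is no power or effect size to reproduce. The only figure is 3 cohorts × 3 patients = 9, which agrees with the n=9 in section 10.4.

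**4. Illustration of the shift.** The inputs below are assumptions; none is in the documents. Let X be the change on the gating test and Y the change on the colour test, both standard normal with correlation rho and no true mean effect. The colour test is done only if X > c. Then

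E[Y | X > c] = rho × φ(c) / (1 − Φ(c)).

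With half the patients passing, c = 0 and the factor is 0.399 / 0.5 = 0.80. With 20% passing it is 1.40, and with 70% passing 0.50. The expected colour change among those tested, in SD units, is:

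| Share passing | rho 0.3 | rho 0.5 | rho 0.7 |
|---|---|---|---|
| 20% | 0.42 | 0.70 | 0.98 |
| 50% | 0.24 | 0.40 | 0.56 |
| 70% | 0.15 | 0.25 | 0.35 |

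If all nine are tested, the expected value is 0 for every rho. A simulation of 200,000 trials of nine patients with the gate at zero gave mean shifts of 0.238 (rho 0.3) and 0.398 (rho 0.5). The observed mean was above zero in 70% and 82% of those trials, against 50% with everyone tested. At rho = 0 there is no shift.

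**5. Number tested.** The expected number is 9 × share, or 1.8, 4.5 and 6.3 patients at 20%, 50% and 70%. The chance that all nine are tested is share⁹, which is at most 0.7⁹ = 4%. The chance that two or fewer are tested is 74%, 9% and 0.4%.

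**6. Illustration without normality.** Suppose three of nine patients truly respond and the other six have no colour change. Suppose the gate passes 80% of responders and 20% of the rest. The share tested is 3/9 × 0.8 + 6/9 × 0.2 = 0.40, or 3.6 patients. The mean among those tested is 0.267 / 0.40 = 0.67 of the responder effect. The true full-cohort mean is 0.33.

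**The case against.** The best reply is that section 8.2 schedules these tests without the condition. If staff follow it, the selection does not arise for anomaloscopy or the Cambridge test up to D365, or for colour constancy at D180 and D365. That stands: the bias depends on the flowchart being followed, and what is certain is the conflict between the two schedules.

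Three further points also stand.

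- These are three of 14 exploratory secondary endpoints, with no test or decision rule, and the primary safety endpoint is untouched. Individual line charts for nine patients would make gaps visible.
- The normal model is a convenience. Section 1.1.1 describes complete colour blindness, so many patients may sit at the floor of these tests.
- If the correlation arises from learning or effort common to both eyes, the treated-minus-fellow difference would remove much of it.

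A reader might infer that patients who do not improve contribute no colour data. The documents do not support this. All three tests are marked at screening for everyone. In row 16 the D15 panel carries only footnote f. Chromatic pupillography and the red and green dark-adaptation thresholds are not conditional on improvement. A reader might also extend the point to the optional late laboratory tests, but footnote e does not govern those, and no direction of bias has been shown for them.

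Definitions of previous tests and of improvement, or a rule for untested patients, may stand in the Procedure Manual or a separate analysis plan that is not shown. A definition would make the selection explicit but would not remove it.

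**Conclusion.** The point holds in conditional form. The flowchart and section 8.2 disagree on whether three secondary colour-vision endpoints are measured in everyone after baseline. Under the flowchart version, their planned summaries would rest on a subset selected for improvement and could be labelled n=9 only if every patient passed the gate. The shift is towards benefit if the gating and colour tests are positively correlated. That is plausible, since they examine function in the same treated eye, but it is not shown in the documents.

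The figure of about 0.8 × rho SD illustrates the mechanism and is no estimate for this trial. It rests on an assumed correlation, normal changes, a gate that half the patients pass, and no true effect. It would be wrong to conclude that the trial's colour results are biased by a known amount, or that the bias is certain.

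**What to change.** Delete footnote e and reconcile rows 14 to 16 of the flowchart with section 8.2. Do colour constancy, anomaloscopy and the Cambridge test (D15 if that is not feasible) in both eyes of all patients at the visits section 8.2 already lists, and at least at screening, D180 and D365. Record inability to perform a test as a result instead of leaving the value missing. Report the number tested at each visit beside every mean, difference and scatter plot. If tests have already been skipped under the footnote, list the patients concerned and do not present the summary as a full-cohort result.

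The cost is one flowchart amendment and modest extra test time for patients who have not improved, at visits where section 8.2 already foresees these tests.
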